
**Study Procedure**

**Overview:** We will recruit Ugandan children aged 6-59 months with anemia (hemoglobin 5 – 9.9 g/dL) and with clinical evidence of malaria who present to the Paediatric Assessment Center and the Paediatric Acute Care Unit at Mulago Hospital in malaria-endemic Kampala, Uganda. All children will be treated for malaria, and any child found to be iron-deficient [erythrocyte protoporphyrin (EP) ≥ 80μmol/mol heme] will be randomized to start a 4-week course of daily iron therapy (2 mg/kg) immediately on Day 0 (immediate group) or 4 weeks later on Day 28 (delayed group). All children will return to the hospital on Day 56 for final assessment (**Figure 1**). To determine the percentage of oral iron incorporated into red blood cells on Day 0 and Day 28, all children will be given an oral dose of iron stable isotope, 57Fe, on Day 0 and an oral dose of a different iron stable isotope, 58Fe, on Day 28. Calculation of isotopic enrichment of the red blood cells 28 days after dosing will permit comparison of red blood cell iron incorporation at the time of initial administration of the iron supplement between the treatment groups (Day 0 incorporation for immediate group vs. Day 28 incorporation for delayed group, Aim 1). Comparison of the change in hemoglobin and other iron markers (erythrocyte protoporphyrin, ferritin, soluble transferrin receptor, hepcidin, reticulocytes) from Day 0 to Day 56 between treatment groups will enable assessment of how immediate vs. delayed iron impacts long-term hematological recovery and iron status (Aim 2).

Study Recruitment and Enrollment: We will recruit a consecutive sample of 100 children with Hb 5.0-9.9 g/dL and between the ages of 6-59 months who present to the Pediatric Acute Care unit at Mulago Hospital, Kampala, Uganda. The inclusion and exclusion criteria are as follows:

Inclusion criteria:

1.) 6 - 59 months of age

2.) Hemoglobin 5.0 - 9.9 g/dL according to HemoCue

3.) Fever in past 24 hours or temperature > 37.5

1. *P. falciparum* on blood smear at Acute Care Unit
2. Residence < 50 km of study hospital

Exclusion criteria:

1. Impaired consciousness on physical exam
2. Seizure activity prior to or during admission
3. Acute malnutrition
4. Known sickle cell disease

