**Day 0 Procedure:** Children younger than 5 years who present to the Paediatric Assessment Center or Paediatric Acute Care Unit with a positive blood smear will have a finger-prick blood sample for hemoglobin and preparation of Giemsa smear as part of routine care. If hemoglobin is 5.0 – 9.9 g/dL, the Giemsa smear is positive, and the child lives < 50 km from the hospital, the child will be eligible for the study. After informed consent for our research study is obtained (see Informed Consent, below), a venous blood sample will be drawn. Blood samples are routinely drawn on children with this clinical presentation as part of standard of care. After informed consent for our research study is obtained (see Informed Consent, below), drops of whole blood will be dispensed for immediate determination of EP by hematofluorometer (Aviv Biomedical, Lakewood, NJ) and for preparation of a reticulocyte smear. The remaining blood will be sent to Corelab for collection of plasma. Children found to be iron-deficient (EP ≥ 80 µmol/molheme) will be randomized to start 4 weeks of daily iron therapy at baseline, once oral medication can be tolerated (immediate group), or 4 weeks later on Day 28 (delayed group). Any child who is not iron-deficient will not receive iron therapy. Upon enrollment all children will be assigned a randomly generated, unique study identification number that will link clinical forms and samples. Caregivers will be given a clinical follow-up schedule, with dates of bi-weekly home visits and Day 28 and Day 56 hospital visits indicated. On Day 0, participants will be given 2500 USh for transport home. On both the Day 28 and Day 56 visits, participants will receive reimbursement commensurate in value to 15,000 USh. 5000 USh will be given to cover transportation costs to and from the hospital and any cell phone air time needed in the preceding 4 weeks to report illness, and a food package containing oil, rice, and/or sugar valuing 10,000 USh.

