**Informed consent:** Once each eligible child is medically stable, a study representative will conduct the informed consent process. The iron study consent form describing the study, including risks and benefits of study participation, will be presented in either Luganda or English, depending on the parent’s preference. Translators will be available if needed. Study staff will explain that not participating in the study or deciding to stop participation will not jeopardize the child’s care. Copies of signed consent forms will be kept on file at the study research offices at Mulago Hospital.

**Randomization:** A list of 100 random, 3-digit numbers will be computer-generated at the University of Minnesota. These numbers will serve as unique study identification numbers. Treatment group (either immediate or delayed) will be then be randomly assigned to each number, in blocks of four. The treatment group for a particular study ID will be placed in a sealed envelope. Envelopes will be opened sequentially by study personnel at patient enrollment.

**Clinical treatment:** Clinical treatment of all children who are enrolled in the study will be overseen by [name]. Ugandan national guidelines will be followed for treatment of malaria, presently oral quinine for hospitalized patients and artemethar combination drugs for outpatients. Initial labs and testing will be done by study physicians and nurses, but clinical care of all patients will be given by the house staff and attending physicians of Mulago Hospital. Other co-infections and medical problems will be treated according to standard protocols of Mulago Hospital. Thick and thin blood smears will be prepared for all enrolled children to look for malaria parasites and density of parasitemia, calculated using parasites per 200 WBC.

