**Table 1: Power and sample size for Aim 1**

|  | Detectable difference | |
| --- | --- | --- |
| n per group | Power 80% | Power 90% |
| 30 | 5.2 | 6.0 |
| 33 | 5.0 | 5.8 |
| 40 | 4.5 | 5.2 |
| 43 | 4.3 | 5.0 |
| 50 | 4.0 | 4.6 |
|  |  |  |

For our primary outcome for Aim 2 of the change in hemoglobin from Day 0 to Day 56 in the immediate vs. delayed iron groups, we will compare mean 56-day change (Day 56 minus Day 0) in hemoglobin between the treatment groups using a two-sample t-test. Secondary analyses will adjust for baseline characteristics of children, including age, sex, anthropometric indices, and stool helminth count. For our secondary outcome of changes in iron indicators between Day 0 and Day 58, we will compare the mean 56-day change in each iron indicator (EP, ferritin, sTfR, hepcidin) between treatment groups using a two-sample t-test for each indicator. Secondary analyses will adjust for age, sex, anthropometric indices and helminth count.

**Sample size calculations:** Assuming a SD in the mean change in hemoglobin to be 1.5 g/dL and alpha = 0.05, with 50 children in each treatment group, we would have 90% power to detect a difference of 1.10 g/dL in the mean 56-day change in hemoglobin concentration between groups, assuming 20% loss to follow-up.

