**Sampling plan:** We will recruit a consecutive sample of children 6-59 months with anemia (hemoglobin 5-9.9 g/dL) and malaria. This is a group of children that commonly presents to the Pediatric Acute Care Unit at Mulago Hospital. All participants will receive extensive follow-up, including bi-weekly home visits and transportation to the hospital for scheduled visits and for any intervening illness. Within this group of moderately to severely anemic children, no distinction will made based on gender or minority. We will exclude children who live far enough from the hospital that complete follow-up would be difficult; children with hemoglobin < 5 g/dL, as these children receive transfusion upon admission; children who are not anemic (hemoglobin ≥ 10 g/dL), as our project focuses on iron absorption and utilization in anemia; and children with signs of cerebral malaria, including impaired consciousness or recent seizure activity.

**Involvement of special classes of subject:** We will be enrolling anemic Ugandan children aged 6-59 months, as the public health problem of coexisting iron deficiency and malaria infection is greatest at this age and in this part of the world.

**Study group assignment:** All children who are found to be iron-deficient (elevated erythrocyte protoporphyrin) will be randomized to receive iron concurrently with antimalarial treatment, which is the current standard of care, or 4-weeks after anti-malarial treatment. We hypothesize that children receiving delayed iron will exhibit greater long-term hematologic recovery and iron status due to more complete parasite clearance and resolution of inflammation at the time of initial supplement administrations, despite the delayed administration of iron.

All children will receive a single dose of iron stable isotope 57Fe (4 mg) at baseline and 58Fe (1.5 mg) at Day 28. Stable isotopes are a safe and accessible way to measure mineral metabolism. They are used regularly to investigate iron absorption in many vulnerable groups, including premature infants and pregnant women. The 4-week course of iron given to all iron-deficient children will be in the form of liquid ferrous sulphate, at a dose of 2 mg iron per kg body weight, as recommended by the World Health Organization.

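### Transfusion is the stated reason for the 5 g/dL hemoglobin floor, but the criteria exclude it only through a hemoglobin range, so some transfused children can still be enrolled

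*Protocol*

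**What the plan says.** Protocol, Protection Of Human Subjects, Sampling plan, gives one reason for the lower hemoglobin limit: it excludes "children with hemoglobin < 5 g/dL, as these children receive transfusion upon admission". Transfusion is mentioned nowhere else in the protocol.

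The operative criteria appear twice, in the Protocol Overview (Selection criteria) and in Study Procedure (Study Recruitment and Enrollment). Both state the limit as a reading: "Hemoglobin 5.0 - 9.9 g/dL according to HemoCue". Both exclusion lists have four items: impaired consciousness, seizures, acute malnutrition and "Known sickle cell disease".

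The sequence comes from Study Procedure:

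- Children who present "will have a finger-prick blood sample for hemoglobin and preparation of Giemsa smear as part of routine care" (Day 0 Procedure). That reading decides eligibility.
- "Once each eligible child is medically stable, a study representative will conduct the informed consent process" (Informed consent).
- "After informed consent for our research study is obtained (see Informed Consent, below), a venous blood sample will be drawn" (Day 0 Procedure), and EP is then read.
- "Children found to be iron-deficient (EP ≥ 80 µmol/molheme) will be randomized to start 4 weeks of daily iron therapy at baseline" or on Day 28 (Day 0 Procedure).
- The tracer dose follows the baseline draw and a two-hour fast (Isotope administration).

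For the Aim 2 primary outcome, "we will compare mean 56-day change (Day 56 minus Day 0) in hemoglobin between the treatment groups using a two-sample t-test".

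**The concern.** The rationale concerns transfusion; the rule concerns a hemoglobin value. The value stands in for transfusion only if every transfused child presents below 5 g/dL and is measured before the transfusion. Nothing in the criteria ensures either.

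Three quantities are exposed.

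- **EP gate.** Randomization depends on EP of at least 80 µmol/mol heme, which would be read on a mixture of donor and patient cells.
- **Aim 1.** The primary comparison sets Day 0 incorporation in the immediate group against Day 28 incorporation in the delayed group. A transfusion before Day 0 would be expected to weigh more on the Day 0 measurement than on the one four weeks later, so equal frequency in the two arms would not fully cancel it.
- **Aim 2.** Donor hemoglobin present in the Day 0 reading is subtracted directly in the change score.

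Eligibility belongs in the protocol. An analysis plan could not repair this afterwards if the transfusion had not been recorded.

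**Working it through.** **1. Which transfused children can enter, on the text as written**

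| Child | Outcome |
|---|---|
| Below 5 g/dL at presentation, transfused on admission | Screened out: eligibility uses the reading at presentation |
| Transfused at another facility, then presents at 5.0-9.9 g/dL | Meets the listed criteria; the presentation reading is already post-transfusion |
| Presents at 5.0-9.9 g/dL, transfused before consent | Meets the listed criteria; EP and tracer follow the transfusion, but the presentation hemoglobin precedes it |

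In the last two rows EP must still reach 80 µmol/mol heme before the child is randomized. The second row is plausible because the protocol (Collaborating sites) describes the site as Uganda's largest referral hospital. It does not say that referred children arrive transfused.

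**2. The plan's own figure**

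Inputs (Sample size calculations, Aim 2): SD 1.5 g/dL, alpha 0.05 (taken as two-sided), 50 per group, 20% loss, difference 1.10 g/dL. Evaluable per group: 50 × 0.8 = 40.

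Normal approximation: power = Φ(1.10 / (1.5 × √(2/40)) − 1.96) = 90.7%. Two-sample t: 89.95%. The stated 90% reproduces.

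**3. Size of a possible baseline shift**

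The transfused volume and donor hemoglobin are not in the protocol. For illustration only, assume 20 mL/kg at 12 g/dL, which is 2.4 g hemoglobin per kg. The protocol estimates blood volume at 80 mL/kg.

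- Once blood volume has returned to 80 mL/kg: 2.4 / 0.8 = 3.0 g/dL.
- Before it has, for a child at 4.5 g/dL when transfused elsewhere: (4.5 × 0.8 + 2.4) / 1.0 = 6.0 g/dL, a shift of 1.5 g/dL.

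**4. Effect on Aim 2 power**

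Let a fraction f of children, equal in both arms, have their 56-day change shifted by x g/dL, with no carry-over to Day 56. Then SD = √(1.5² + f(1−f)x²). For f = 0.10 and x = 3: √(2.25 + 0.81) = 1.749.

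Power at 1.10 g/dL, 40 per group, normal approximation (t-test in brackets):

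| x (g/dL) | f = 5% | f = 10% | f = 20% |
|---|---|---|---|
| 1 | 90.1% (89.3%) | 89.5% (88.8%) | 88.7% (87.9%) |
| 1.5 | 89.3% (88.6%) | 88.1% (87.3%) | 86.1% (85.3%) |
| 3 | 85.2% (84.4%) | 80.3% (79.3%) | 72.6% (71.5%) |

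Both f and x are assumptions. No comparable calculation is possible for Aim 1 or the EP gate, because the documents give nothing on how transfusion affects them.

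**The case against.** A reader might infer that a child arriving at 4.5 g/dL, transfused and then stable at 7.5 g/dL, meets every criterion. The documents do not support that. The Day 0 Procedure takes the hemoglobin at presentation, consent is sought from children already found eligible, and the sampling plan's exclusion below 5 g/dL can only refer to the value before transfusion. Re-screening after transfusion is not forbidden, but it is not described either. This part of the objection stands.

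A reader might also infer that the Day 0 data are generally contaminated. The only Day 0 hemoglobin described is the finger-prick at presentation. The Protocol Overview and the human-subjects section treat the baseline venous sample as the routine admission draw, whereas the Day 0 Procedure places it after consent. If admission blood is used, a later transfusion would not touch EP. The tracer dose follows consent on either account, and a transfusion before arrival affects everything. The objection therefore narrows the second route and leaves the first open.

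EP is a further gate. If donor blood has normal EP (an assumption), dilution would tend to keep transfused children out of randomization. That reduces their number but does not make the gate a reading of the child's own cells.

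Finally, the protocol gives no transfusion frequency at or above 5 g/dL. A transfusion before randomization adds variance and possible chance imbalance to Aim 2, with no systematic difference expected between arms. That is correct. It is less complete for Aim 1, where the arms are measured on different days. The protocol's Background says hepcidin rises with iron sufficiency and lowers absorption, so a transfusion could depress Day 0 incorporation in the direction of the study hypothesis. This is an inference of unknown size.

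**Conclusion.** The point holds in a limited form. The stated purpose of the 5 g/dL floor is not fully carried out by the criteria: two groups of transfused children can pass, those transfused before arrival and those transfused between a qualifying reading and the post-consent procedures. Children below 5 g/dL at presentation cannot.

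No stated figure is wrong, and the sample size needs no change. If 5-20% of children were affected, the loss of Aim 2 power would be small for shifts of 1-1.5 g/dL and material only near 3 g/dL. The large-shift result should not be read as a forecast: the affected share, the volume, the donor hemoglobin and the absence of carry-over are all assumptions. The second group would not alter the Aim 2 baseline if the presentation finger-prick serves as the Day 0 hemoglobin. This is a cheap improvement rather than a flaw that threatens the trial.

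**What to change.** 1. Add to both exclusion lists (Protocol Overview and Study Procedure): *blood transfusion in the current illness, at any facility, before the Day 0 sample and tracer dose*. The documents offer no basis for a longer look-back window; if the sponsor wants one, it should choose and justify it.
2. State with the hemoglobin criterion that the qualifying HemoCue value is the pre-transfusion value at presentation. This also rules out qualifying on a later reading.
3. Add a case report form item for any transfusion during the study. How such children are analyzed can be left to the statistical analysis plan.

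The cost is one exclusion line, one clarifying sentence and one form item, with a few children lost from recruitment. Clinical care and the planned sample size are unaffected.

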**Potential risks to subjects:**

*Potential risk: Iron therapy*

The primary risk of iron therapy in a malaria-endemic area is the risk of increased episodes of malaria. We will be giving iron only to those children who are iron-deficient. A recent, large, randomized controlled trial in Pemba, Tanzania, showed an increased risk of serious adverse events (hospitalizations and mortality) in children given iron/folic acid. A sub-study revealed, however, that this risk was limited to those who were iron-sufficient and received iron, while children who were iron-deficient (as defined by an elevated erythrocyte protoporphyrin) had significantly *fewer* serious adverse events. We do not expect to see an elevated malaria risk with the WHO-recommended dose that we are giving for several reasons: 1) We are only giving iron the iron-deficient children. These children benefitted from iron in the Pemba study; 2) We will be providing bi-weekly home visits and access to health care, which was not available on the main Pemba study; 3) We will instruct caregivers to provide the iron with a small amount of food. No instruction with regard to timing of food intake was given in the Pemba study, and it is possible that concurrent consumption of food would slow the “bolus” absorption imposed by a large dose of supplemental iron given by itself. Such a bolus dose has been hypothesized to increase the amount of free, or non-transferrin-bound iron which may exacerbate existing malaria; and 4) Unlike the Pemba study, we will not be giving folic acid, which can reduce the efficacy of certain anti-folateantimalarials, including sulphadoxine-pyramethamine, the antimalarial used in the Pemba study. For all of these reasons, we believe the risk of serious adverse events due to iron therapy is low in our population.

The potential risks described above pertain primarily to the daily, liquid ferrous sulphate syrup that each iron-deficient child will receive for 4 weeks. The amount of iron given in the stable isotope form is minute compared to the daily supplemental amount and unlikely to cause any adverse effects. Stable isotopes are naturally occurring forms of a mineral, in this case iron, which can be used as a tracer in the body. There are no known risks to the stable isotopes.

In any setting, iron may be associated with gastrointestinal distress. We will monitor this side-effect through parental reports in bi-weekly home visits and discontinue therapy if discomfort persists. All potential side-effects will be monitored by the study’s DSMB (see DSMB below).

*Potential risk: Lab test collection:* The study protocol calls for three venous blood draws—one at baseline, one at Day 28, and one at Day 56. The baseline blood draw is part of the routine care for any admitted patient with severe anemia and malaria. The only risk to study participants are those of venipuncture, including persistent bleeding, pain, or infection. Experienced nurses and medical officers will ensure that all testing is done in a sterile manner. We have documented no significant side effects from the venipuncture we have done previously at Mulago Hospital, so we do not consider this testing to be of significant risk to the study subjects.

**ADEQUACY OF PROTECTION AGAINST RISKS**

**Plans for recruitment and informed consent:** Study participants will be recruited in the Pediatric Acute Care Unit of Mulago Hospital. Informed consent will be obtained from parents or guardians of all study participants, with information on risks and benefits being provided and consent forms being given to the parents or guardians in the local language. Data will be stored in a locked office accessible only to study personnel. Caregivers of potential participants will be informed that their child can leave the study at any time without jeopardizing the care they will receive at Mulago Hospital. No study-specific tests will be administered before informed consent is obtained.

**Circumstances of consent:**Consent will be sought and obtained from caregivers bringing eligible children into the Pediatric Acute Care Unit. Once the patient is medically stabile, the Medical Officer on duty will approach the caregiver and inform him or her about the study and will provide a full description of risks and benefits of study participation. The consent form will be available in both English and Luganda, the local language. The caregiver will acknowledge consent by signing the form.

**Plans for protection against risk:**

*Iron therapy:* Bi-weekly home visits will be made for every study participant. At these home visits, any ill child, including those with clinical signs of malaria, will be referred and given transportation to Mulago Hospital for care. Any child with smear-confirmed malaria infection will receive treatment. Transportation and treatment are provided free of charge. At biweekly home visits, study monitors will also verify that the iron is taken appropriately, will record any outside clinic visits, and will monitor any adverse events. A Data Safety and Monitoring Board (See DSMB, below) will be established to ensure human subjects’ protection throughout the study period.

*Blood draws:* Experienced nurses and medical officers will ensure that all testing is done in a sterile manner. We have had no adverse events from blood draws in any previous or ongoing studies at Mulago.

**Plans for medical or professional intervention:** Any enrolled child found to be ill during the study period will receive both transportation to the hospital and medical care free of charge. To ensure the safety of trial participants, study investigators are monitoring, recording, and reporting both adverse events and serious adverse events. An adverse event (AE) will be defined as any untoward medical response to the iron therapy itself, including, but not limited to, constipation, abdominal pain, and diarrhea. These symptoms will be recorded by home monitors. Home visit forms will be returned to the study office and reviewed by study medical officers on a daily basis. A *serious adverse event* is any untoward medical occurrence that happens after initial hospitalization and discharge that results in death, is life-threatening, requires hospitalization, or involves a substantial overdose of iron (consumption of more than 10 times the prescribed dose at a single time*)*.

In the event of a serious adverse event, the study medical officer will be notified immediately and will complete a Serious Adverse Event Reporting form. A copy of this form will be placed in the child’s folder and another copy will be placed in a SAE folder, to be kept in the office. The Medical Officer will also inform the site PI of the SAE within 48 hours. The site PI will then inform the U.S. PI, ideally within 48 hours, but in no more than 7 calendar days. The U.S. PI will relay SAE information to the DSMB chair in no more than 15 calendar days from the time of the event. The PIs will also submit periodic reports of all SAE’s (quarterly for Makerere University School of Medicine Research Ethics Committee, yearly for University of Minnesota Institutional Review Board.)

If a subject is withdrawn because of a serious adverse event that does not result in death, the subject will be followed and treated by the medical officer until the abnormal parameter or symptom has resolved or stabilized.

**Potential benefits of the research:**With the proposed study, children with elevated erythrocyte protoporphyrin will receive a 4-week course of ferrous sulphate. Improvement in iron status has been associated with improved neurobehavioral development in numerous studies, and giving iron to children with elevated erythrocyte protoporphyrin living in malaria-endemic areas has been shown to be protective against hospitalizations and mortality. Enrolled children will have no direct benefit from the hematologic and isotopic studies done, but will have minimal risk from these studies. Free health care and transportation to Mulago hospital will be provided to all enrolled children for any illness in the course of the study.

**Relationship of risks to anticipated benefits:** The risk of iron therapy in malaria-endemic areas is likely confined to those children who are not iron-deficient, as described above. We do not believe that the WHO-endorsed dose of iron that we are providing to iron-deficient children will impose a risk. Rather, we believe that the iron will be protective against serious adverse events and perhaps will help to ensure improved neurobehavioral development. The risk of complications from venipuncture is also small in comparison to the established benefit of providing iron to iron-deficient children.

**Importance of the knowledge gained:** The present study will provide important and direct physiologic evidence of the best sequencing of iron and anti-malarial treatment for iron-deficient children living in malaria-endemic areas. Delaying iron until after resolution of inflammation and parasite clearance may result in better absorption, thus increasing the efficacy of iron therapy. This information will help guide malaria and iron intervention programs and potentially help to improve neurobehavioral development of millions of children, as iron deficiency and malaria coexist in many regions of the world, including sub-Saharan Africa, Southeast Asia, and Central and South America.

**Relationship of risks to the knowledge gained:** Iron deficiency is an established cause of cognitive impairment. Establishing direct, physiological evidence for the best sequencing of interventions has the promise to improve millions of lives and may in fact lessen any risk of giving iron in malaria-endemic areas.

**Data and safety monitoring plan:** A Data Safety Monitoring Board will be established to provide external, objective advice regarding the safety and efficacy of the administered interventions. The Board will be comprised of experts in clinical trials, biostatistics, iron, and child health, as well as one lay person. At least one Board member will be Ugandan. Board members will be independent from the study and will meet in open and closed sessions at the start of the study, when half of the expected number of children have completed the study, and at the completion of the study to evaluate study data and provide recommendations pertaining to participant safety and trial conduct to investigators.

While the DSMB will meet at these appointed times to review SAE’s, to advise on issues of protocol adherence, to review recruitment and follow-up rates, and to advise the investigators on pertinent safety issues, formal stopping rules are not in place for this study on account of the small sample size and resulting limited power for an interim analysis to make meaningful comparisons between treatment groups. We have the same treatment groups (immediate and delayed iron) in more severely ill children (cerebral malaria or severe malarial anemia) in our ongoing, larger (n=300) U01 study at Mulago Hospital and have not observed SAE differences that exceed stopping rule thresholds in that study to date.

**ClinicalTrials.gov requirements:** The proposed study has been registered with ClinicalTrials.gov by the PI, as required. Updates regarding recruitment status or protocol changes will be made in a timely manner.

